The primary health care level, especially the HWC, offers an opportunity to bridge this gap by bringing the CRD screening and diagnosis closer to the community. With appropriate training and supportive supervision, the ASHA workers can identify the suspected CRD patient by measuring their peak expiratory flow rate. The Peak Expiratory Flow Rate (PEFR) has demonstrated effectiveness in suspecting conditions such as COPD and asthma, particularly in resource-limited settings (12, 15, 16). It can be proposed that a spirometry technician or ANM be trained to conduct spirometry tests at health and wellness centers (HWC), and that the community health officer (CHO) in charge of the HWC may interpret the results and diagnose CRDs after intensive training and telemedicine support for interpretation of the report. Provision of diagnostic (spirometers) and drugs at the health and wellness center will be desirable, as mentioned in the district program implementation plan by the state government (12, 17, 18)

Evidence from international and primary care models supports the feasibility of this approach. Brazil's Family Health Strategy (FHS) and South Africa's PACK program have demonstrated the value of integrated, guideline-based, team-delivered care for the chronic disease, including asthma and COPD (19, 20). The Global Alliance against Chronic Respiratory Diseases (GARD) has also emphasized strengthening health systems to prevent and control CRDs through primary health care (21). In India, two models are implemented for the screening and diagnosis of the CRDs through the primary health care. The SWAAS (Stepwise approach to airway diseases) program has demonstrated that active screening and early management of airway disease at the primary health care level can be feasible and potentially a cost-saving alternative to the current passive approach (22). Similarly, community-based initiatives using portable point-of-care spirometry in the Nashik district of Maharashtra's Dindori block have demonstrated operationally feasible, large-scale screening, diagnosis, and management of COPD and other chronic respiratory conditions outside tertiary care settings (23).

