Together, these findings support the suggestion that a decentralized, primary care-based model for CRD screening and diagnosis may help address delayed diagnosis and improve access to chronic care in rural settings and emerge as a logical strategy for facilitating early detection of CRDs. However, evidence on the feasibility, implementation logistics, and operational evaluation of such models in routine primary health care settings remains limited.

The existing scientific literature provides substantial evidence to support the hypothesis that following a structured implementation model may be successful, which includes integrating community-based screening by Accredited Social Health Activists (ASHAs) using peak flow meters (12, 15, 16). and diagnostic confirmation at Health and Wellness Centres (HWCs) via spirometry. This model will enhance early detection and contribute to the strengthening of primary health care guidelines for COPD and asthma management. Although current CRD guidelines at the primary care level offer a supportive framework for such an intervention, the proposed model is poised to provide greater accessibility compared to existing approaches. The comparison of the guidelines and the proposed model is described in Table 1. With guidelines in place, yet a lack of clear implementation strategies at the ground level, it offers a timely and strategic opportunity to rigorously explore the feasibility of this model.

**Table 1 T1:** The comparison of existing guidelines and the proposed ‘***SHVASAN***’ model.

Health facility	Key person involved	Existing guidelines Activities National Program for Prevention and Control of Cancer, diabetes, cardiovascular diseases, and Stroke, 2021 (14)	Proposed ‘***SHVASAN***’ model Activities
Beneficiary -Age 30 years and above			
At the community level	ASHA	Fill up a community-based assessment (CBAC)checklist for the above 30-year-old population with two relevant questions for risk factors of COPD Referral for the at-risk population to HWC- PHC and for other NCDs	- ASHA fill up the Risk Assessment for COPD and Asthma form for the above 30-year-old population - Mmrc - Cough assessment - PEFR measurement - Referral of suspected at HWC - Follow up of the patient put on treatment for inhalation techniques when diagnosed

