A Feasibility index document tool is being developed using the Delphi technique. That will include feasibility dimensions: Technical, Operational, and Resource- All three dimensions would be measured using study tools. The COPD-Asthma screening questionnaire: Existing pretested and validated questionnaires assessing the risk factors and exposures, such as smoking, use of biomass fuel, family history, quality of life, and medical history, as well as known cases of COPD or Asthma in the eligible population. The Peak exploratory flow rate (PEFR) skills, screening of the population, will help calculate the technical feasibility. That may be reflected through the number of suspected cases, the recruitment rate, the retention rate, and the screening rate.The COPD-Asthma diagnosis proforma: An existing, pretested, and validated proforma will be used to diagnose suspected cases. It will be filled by CHO at HWC. The proforma will document the medical history, symptoms, comorbidities, treatment, and vital clinical measurements such as blood pressure, blood oxygen level, Pulse, etc. Related and other pertinent clinical findings will be noted. A pre- and post-spirometry reading and interpretation in accordance with the NPCDCS 2021 guidelines, the categorization of COPD and asthma will be documented in the same proforma. This will also help calculate the technical feasibility of the diagnosis.The PEFR checklist for skills assessment of ASHAs would be completed by the investigator at two time points: after the training and during field data collection by ASHAs.Spirometry testing activity checklist for the skill assessment during the conduction of the test at HWC.Data Quality Checks
Data collection –for the quantitative data, Quality checks will be conducted while collecting data at the community level. Quality checks would be conducted randomly on at least 5% of the sample.Quality checking for the Peak flow meter skill can be done using the checklist to be filled out by the field senior supervisorsA Spirometry quality checklist will also be filled out every time of the observation.Random quality checking visits will be planned by technical experts for PEFR and Spirometry testing.

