Quantitative - Data will be entered in Microsoft Excel and then imported to SPSS (version 27) for Windows package (IBM SPSS Statistics for Windows, Version 25.0. Armonk, NY: IBM Corp). The proportions of categorical variables of interest (Respondents with COPD-Asthma diagnosis in both PHCs) will be compared using the Chi-Square test. Means of variables of interest (time for symptoms, diagnosis, age, severity of disease) will be compared using the independent t-test. The associations between disease proportion and PEFR and spirometry values will be determined using the chi-square test. A multivariate logistic regression analysis will be carried out to identify significant predictors using PEFR values in implementing PHCs.Qualitative analysis -Data from IDIs and focus group discussions will be transcribed and thematically analyzed, and if required, MaxQDA software may also be used. In-depth interviews and focus group interviews will be transcribed verbatim, checked, and corrected if required. The transcripts will then be thematically analyzed. The transcripts will be independently read to become familiar with the material. The notes on insights and patterns from the transcripts will be derived. Subsequently, participants and/or the guide may engage in discussion to reach a consensus on the content. Coding transcripts using code labels closely linked to the meaning of the quotes, and organizing codes with similar content into groups and themes, would generate initial themes. Groups and initial themes were then presented and discussed with the guide. Then, if suitable, the Normalisation Process Theory (NPT) (27) will be used as a theoretical lens to understand how the implementation of codes and initial themes, organized within the constructs of NPT, were reviewed before being refined and delineated into four main themes. In cases where themes overlap with more than one NPT construct, a best-fit choice will be made. The content will be finalized thematically later.The comparative analysis of data from both PHCs would be done using the chi-square test for characteristics of diagnosed cases. The number of newly diagnosed cases during the study period would be obtained from the Public Health Management Information System (HMIS)Feasibility index - Based on qualitative and quantitative data collection and analysis, the feasibility dimensions will be scored and finalized through Delphi consensus. The feasibility index may be derived from the scores and the assigned weights.

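### Testing diagnosis against spirometry is circular, and the PEFR–disease analyses can be inflated unless they are confined to people who had spirometry

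*Protocol article*

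**What the plan says.** Two sentences of the quantitative analysis plan (Protocol article, Plan for analysis, printed under Qualitative component) are at issue. The first is "The associations between disease proportion and PEFR and spirometry values will be determined using the chi-square test". The second is "A multivariate logistic regression analysis will be carried out to identify significant predictors using PEFR values in implementing PHCs". The second names neither the dependent variable nor the people to be analysed.

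The article says how disease status arises. The Introduction describes "diagnostic confirmation at Health and Wellness Centres (HWCs) via spirometry", and Table 1 lists spirometry as the diagnostic test at the HWC and the PHC. Under Quantitative component, one proforma carries both the reading and the diagnosis: "A pre- and post-spirometry reading and interpretation in accordance with the NPCDCS 2021 guidelines, the categorization of COPD and asthma will be documented".

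It also says who gets that work-up. In the Introduction, "the ASHA workers can identify the suspected CRD patient by measuring their peak expiratory flow rate". In the community row of Table 1, the ASHA completes the risk form, mMRC and cough assessment, and then comes "PEFR measurement - Referral of suspected at HWC". The diagnostic step is for people already suspected: "An existing, pretested, and validated proforma will be used to diagnose suspected cases". Study design lists a cascade from screened to suspected, referred, reaching the HWC and diagnosed.

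**The concern.** There are two separate problems.

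- **Spirometry.** If the spirometry reading fixes the category of COPD or asthma, diagnosed and undiagnosed people must differ on spirometry. A significant chi-square says nothing about prediction, data quality or the model's performance.
- **PEFR.** PEFR helps select who receives the reference test. People who screen negative, and referred people who do not attend, have no verified status. An analysis over everyone screened has to give them one. If that is disease-free, cases with a normal PEFR disappear from the diseased group and PEFR looks more strongly related to disease than it is. This is partial-verification bias.

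PEFR measurement by ASHAs is a core part of the model, and the Discussion looks ahead to policy recommendations and wider rollout. An inflated PEFR–disease association could be read as support for the screening step when the design cannot provide it.

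**Working it through.** **The plan's own figure.** The only calculated figure is the sample size for one prevalence (Quantitative component): p = 0.08, d = 0.008, 95% confidence. n = 1.96² × 0.08 × 0.92 / 0.008² = 4,417.8, so 4,418; doubled, 8,836. Both reproduce. The point does not depend on them; they supply only N and the 8% used below.

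**Spirometry.** No arithmetic is needed. The proforma records the COPD or asthma category together with the spirometry reading and its interpretation. The analysis plan then tests that category against spirometry values. One side of the comparison is derived from the other.

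**PEFR, by hand.** Suppose PEFR is unrelated to disease (true odds ratio 1.0), prevalence is 8%, and everyone with a low PEFR is tested. Let q be the share of cases with a normal PEFR who still reach spirometry because of symptoms or risk factors. The article does not give q, so a range is shown. If untested people count as disease-free, the apparent odds ratio is

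(0.08 / 0.92) ÷ (0.08q / (1 − 0.08q)) = (1 − 0.08q) / (0.92q).

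- q = 1: 0.92 / 0.92 = 1.0
- q = 0.75: 0.94 / 0.69 = 1.36
- q = 0.5: 0.96 / 0.46 = 2.09
- q = 0.25: 0.98 / 0.23 = 4.26

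**PEFR, by simulation.** N = 8,836, prevalence 8%, 100 replicates per scenario. Assumptions that are not in the article: a standardised low-PEFR score; the lowest 20% of PEFR flagged; a yes/no symptom correlated with PEFR and raising the log-odds of disease by 1.0. The entries are mean odds ratios per SD of low PEFR.

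| Who is tested | Handling in the logistic model | Truth 1.0 | Truth 2.0 |
|---|---|---|---|
| Everyone | symptom included | 1.00 | 2.00 |
| Low PEFR only | tested only, symptom included | 0.99 | 1.96 |
| Low PEFR or symptom | tested only, symptom included | 1.01 | 2.03 |
| Low PEFR or symptom | tested only, symptom left out | 0.78 | 1.58 |
| Low PEFR only | untested coded disease-free, symptom included | 4.49 | 6.99 |
| Low PEFR or symptom | untested coded disease-free, symptom left out | 2.02 | 3.85 |
| Low PEFR and symptom | untested coded disease-free, symptom left out | 4.84 | 6.43 |

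With a true odds ratio of 1.0, each of the last three rows was significant in 100% of runs, and the 0.78 row in 98%. In the last two rows the symptom is also omitted, so part of the excess is ordinary confounding. The row with the symptom included shows that coding untested people as disease-free inflates the estimate without it.

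**The case against.** The strongest reply is that the PEFR problem needs a step the article never states. It does not say that untested people will be coded disease-free, and a journal article may leave the regression's outcome and population to a fuller plan. The wording could even mean that PEFR is the dependent variable. Selecting people on a covariate that is in a correctly specified logistic model does not bias that covariate's odds ratio, as the tested-only rows with the symptom included show. All of this stands, and it makes the PEFR half conditional. It does not remove it: the article sizes the study for prevalence in 8,836 adults and lists prevalence as a secondary outcome, so everyone screened is a natural denominator, while only suspects are worked up.

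A reader might go further and infer that the PEFR predictors are bound to be artefacts, with an infinite odds ratio and an apparent sensitivity of 100%. That would require referral on PEFR alone (q = 0 above). Table 1 lists the risk form, mMRC and cough assessment beside PEFR, so people with a normal PEFR can be referred and diagnosed.

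Nor does the circularity carry over in full to PEFR. PEF below 80% predicted enters a provisional asthma diagnosis only in the existing-guideline column of Table 1, not in the SHVASAN column. Categorising PEFR for a chi-square loses information but is not an error in itself.

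It is also fair to say that neither analysis feeds the primary outcome, and that the article does not plan to estimate the accuracy of PEFR. That limits the consequence. It does not help the spirometry test, which no fuller plan could make informative.

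**Conclusion.** The concern holds in two parts of different strength.

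The disease-by-spirometry test is circular by construction. This follows from the article's own description of diagnosis and rests on no outside assumption.

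The PEFR analyses are open to partial-verification bias, and whether it occurs depends on choices the article leaves open. If untested people count as disease-free, a true odds ratio of 1.0 becomes about 2.0 to 4.8 and 2.0 becomes 3.9 to 7.0. Those figures rest on the simulation's assumptions about referral, the PEFR cut and the symptom; the hand calculation shows how the size moves with the referral rule. If only tested people are analysed but a symptom that drives referral is left out, the bias runs the other way (1.0 becomes 0.78; 2.0 becomes 1.58). With tested people and the referral variables in the model, it is negligible.

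The change should be made, but these are supporting analyses and the feasibility index does not rest on them.

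**What to change.** - Delete the test of disease against spirometry values. Report spirometry values descriptively by diagnosis.
- State that disease is the outcome of the logistic regression, and fit the PEFR analyses only in people with usable spirometry.
- Keep PEFR as a continuous percentage of predicted. Include every variable that drives referral: mMRC, cough assessment, and risk-form items such as age, smoking, biomass fuel and family history. Risk-form items without mMRC and cough are not enough, as the 0.78 result shows.
- Do not code untested people as disease-free, whether they screened negative or were referred and did not attend.
- Report the positive predictive value of ASHA referral: confirmed cases divided by people with spirometry done.
- Limit the conclusions to people who were referred and tested.

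The cost is a change of analysis wording. The model will contain fewer people, its estimates will be less precise, and its conclusion will be narrower: it will not describe how PEFR performs in everyone screened.

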## Methods and analysis

### Study design

This will be a mixed-methods implementation study to assess the feasibility of the ***SHVASAN*** model for screening and diagnosing COPD and asthma at the primary health care level.

The study will include the following components:

First, a longitudinal quantitative component in the implementing PHC to assess the feasibility of implementing the ***SHVASAN*** model over the study period from the initial implementation. Implementation will begin with the training of ASHAs, CHOs, and equipment will be provided for setting up the screening and diagnosis across the Male PHC in Pune district, India. All 35 villages and ASHAs would be screening the population above 30 years of age. And CHOs across all Health and wellness centres (06 + 02 at PHC and one at RH) will diagnose the CRDs. The longitudinal quantitative component will include the number screened, number suspected, number referred, number reached the HWC, number underwent and received a diagnosis, number put on treatment, and number followed up. Second a Delphi technique to obtain expert consensus on the following components: Technical feasibility, Operational feasibility, resource feasibility (including indicators), Measurement strategy, measurement scoring, and appropriate data sources for each feasibility dimension, and finalising ***SHVASAN*** characteristics. This involves finalizing the intervention package and assessing the expert opinion for feasibility indicators. The third qualitative component is embedded in the longitudinal quantitative component. This includes a focused group discussions (FGDs), which will be undertaken among the key stakeholders to inform quantitative implementation of the ***SHVASAN*** model. Fourth, the analytical cross-sectional component will be conducted to compare the proportions of newly diagnosed COPD and asthma cases among adults aged 30 years and above over one year between the implementing and the adjacent PHC using routine Health Management Information System (HMIS)data. This component will help assess whether implementing the ***SHVASAN*** model is associated with improved case detection for COPD and asthma compared to routine NCD implementation. The explanatory sequential component with qualitative methods to explore the facilitators, barriers, acceptability, accessibility, and operational challenges associated with the implementation of the ***SHVASAN*** model, including the stakeholders such as medical officers (MO), community health officers (CHO), ASHA, and participants above the age of 30 years.

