**Figure 2 F2:**
[figure not shown]
‘***SHVASAN***’ study setting- Mulshi Block, Pune District Maharashtra, India.

The implementing site will be the *Male* PHC*,* where the ***SHVASAN*** model will be implemented and assessed for feasibility. The total population of *Male* PHC is 12,148 adults aged 30 years and above residing in 35 villages. The health care infrastructure includes eight HWCs, including one at the primary health center and one at the Paud rural hospital. An adjacent PHC from the same block, namely *Maan* PHC, will be selected as a non-implementing PHC for the secondary comparative objective. The Maan PHC is similar to Male PHC with respect to geographic, socio-demographic, cultural, environmental, and health care system context. It will continue routine providing services and will be used only to compare the proportions of newly diagnosed COPD and asthma cases among adults over a one-year study period.

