### Quantitative component

Sample Size estimation for quantitative component: The sample size calculation is based on an estimated prevalence of COPD of 8% (1, 2). Considering an allowable error (d) of 0.8% (10% of the prevalence) and a 95% confidence level, the required sample size for the study is 4,418 adults. For the non-probability sampling technique, a design effect of 2 is applied to account for potential loss to follow-up. Thus, the final sample size is 8,836 adult participants.

Inclusion criteria – Permanent residents, are of age 30 years and above, and are ready to consent. Implementation stakeholders (ASHA, CHOS, MO, Community representatives from implementing PHCs, Taluka health officer, District health officer) are ready to consent

Exclusion criteria: Terminally ill adults

Research Tools: Quantitative tools will be used to calculate the feasibility index for the ***SHVASAN*** model.

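### The planned logistic regression names no allowance for clustering by village or ASHA, so p-values for predictors that vary at that level may be too small

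*Protocol article*

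**What the plan says.** The Quantitative part of the Plan for analysis lists its methods in order: chi-square tests, independent t-tests, a further chi-square test, and then a regression. Of the last it says: "A multivariate logistic regression analysis will be carried out to identify significant predictors using PEFR values in implementing PHCs". The outcome and the list of predictors are not spelled out, and no cluster term, random effect or robust variance is named.

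The structure of the data is given elsewhere.

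- Study design: "All 35 villages and ASHAs would be screening the population above 30 years of age".
- Study design, on diagnosis: "CHOs across all Health and wellness centres (06 + 02 at PHC and one at RH) will diagnose the CRDs". This adds up to nine centres, whereas Study setting counts eight.
- Study setting: "The total population of *Male* PHC is 12,148 adults aged 30 years and above residing in 35 villages".
- Quantitative component, sample size: "a design effect of 2 is applied to account for potential loss to follow-up". The same sentence also ties the factor to non-probability sampling. It does not mention villages or ASHAs.

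**The concern.** The ASHA takes the PEFR reading and completes the questionnaire, so readings within a village share an operator and a setting. The protocol itself treats operator skill as something that may vary: skill in performing PEFR is a feasibility indicator in Table 2, and each ASHA is to be checked after training and again in the field. Exposures such as biomass fuel may also be shared within a village. If the outcome varies between villages as well, an ordinary logistic regression counts correlated adults as separate evidence.

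The stated purpose of the model is to pick out significant predictors. What is at stake is therefore whether a predictor labelled significant has earned the label, chiefly where that predictor follows the village or the ASHA.

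**Working it through.** **1. The plan's own figure.** With p = 0.08, d = 0.008 and z = 1.96, n = z²p(1−p)/d² = 3.8416 × 0.0736 / 0.000064 = 4,417.8. This rounds up to 4,418, and 2 × 4,418 = 8,836. Both stated figures reproduce.

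**2. Cluster size.** If all 8,836 adults enter the model, m = 8,836/35 = 252.5 per village.

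**3. Predictor constant within a village.** The design effect is DEFF = 1 + (m−1) × ICC, with the ICC on the observed (0/1) scale. The true SE is √DEFF times the ordinary one. The true type I error of a nominal 5% test is 2 × [1 − Φ(1.96/√DEFF)]. The ICCs are assumptions.

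| Assumed ICC | DEFF | SE ratio | Type I error |
|---|---|---|---|
| 0.001 | 1.25 | 1.12 | 8% |
| 0.005 | 2.26 | 1.50 | 19% |
| 0.01 | 3.51 | 1.87 | 30% |

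**4. Predictor that varies between individuals.** Approximately, DEFF = 1 + (m−1) × ICC of outcome × ICC of predictor. With outcome ICC 0.01 and predictor ICC 0.05, DEFF = 1.13, the SE ratio is 1.06 and type I error is 6.5%. With predictor ICC 0, DEFF is 1 and the test keeps its 5%.

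**5. Simulation.** Ordinary logistic regression was fitted to 35 clusters of 252 with a base rate of about 8% and a predictor with no true effect, 400 replicates per setting. The outcome ICC is on the latent scale. It converts to the observed scale as roughly p(1−p) × σ², where σ² = ICC/(1−ICC) × π²/3. Latent 0.02 gives 0.0736 × 0.067 = 0.005, and latent 0.05 gives 0.0736 × 0.173 = 0.013.

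| Predictor ICC | Type I error, latent ICC 0.02 | Type I error, latent ICC 0.05 |
|---|---|---|
| 0 | 3.5% | 4.8% |
| 0.05 | 5% | 4.8% |
| 0.2 | 7% | 12% |
| 1 (village-constant) | 18% | 40% |

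The Monte Carlo standard error at 5% is √(0.05 × 0.95/400) = 1.1 percentage points, so the first two rows are compatible with 5%. The simulated 18% agrees with the 19% from the formula at observed ICC 0.005.

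**6. Fewer adults in the model.** If the outcome is spirometry diagnosis and 20% of the adults are tested (an assumption), m is about 50. At ICC 0.01 DEFF is about 1.5, and type I error is about 11% even for a village-constant predictor.

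**7. Doubling n does not help.** At 4,418 adults m = 126.2, and ICC 0.01 gives DEFF = 1 + 125.2 × 0.01 = 2.25 and type I error of about 19%. At 8,836 adults the figures are 3.51 and 30%. Larger clusters in the same 35 villages increase the inflation in an unadjusted model.

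**The case against.** The strongest reply is that this rests on silence. The article does not say that adults will be treated as independent. A condensed article commonly leaves variance estimation for a supporting regression to an analysis plan, and that plan is not shown. This stands as a limit on the point: no error has been demonstrated. It does not remove the point, because the article names its methods one by one, and each in its standard form assumes independence.

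Several stronger readings are tempting, and the documents do not support them.

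- *All the standard errors are too small.* The smoking, family history and medical history items are recorded per person, and for predictors with little village clustering the simulated error stays near 5%. No predictor constant within villages is named.
- *The factor of 2 is the plan's own allowance for clustering.* It would correspond to an ICC of 1/251.5 = 0.004, but the protocol attributes it to the sampling technique and to loss to follow-up. That ICC cannot be credited to the plan.
- *Each ASHA covers one whole village.* The number of ASHAs is not clearly given.
- *Spurious predictors will drive rollout.* The primary outcome is the feasibility index. The secondary outcomes are facilitators, challenges and prevalence. None depends on this regression, and the Discussion rests its policy case on yield, cost and acceptability.
- *Descriptive proportions also need clustered standard errors.* All 35 villages are included, and 8,836 is 73% of the 12,148 eligible adults. For a description of this PHC, between-village variation is arguably not sampling error, so the point is confined to the regression.

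**Conclusion.** The point holds in a limited form. The data are nested by the protocol's own account, and the named regression carries no allowance for it. Run as named, it may understate uncertainty for predictors that follow the village or the ASHA, and it is close to correct for those that vary mainly within villages.

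The figures of 19% to 30% are conditional on an assumed observed-scale ICC of 0.005 to 0.01, on all 8,836 adults entering the model, on 35 equal clusters, and on a predictor constant within villages. Relaxing either the second or the last of these brings the inflation down, often to little. Any further clustering by diagnosing centre has not been sized here. Since the analysis is supportive, this is a cheap improvement of low priority.

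**What to change.** Add a sentence to the Plan for analysis stating that the logistic regression will take the village or ASHA as the cluster, using whichever is the larger unit if they do not coincide. Either GEE or cluster-robust standard errors, with a small-sample correction for about 35 clusters, or a random intercept would serve. The choice should be stated, because the two approaches give odds ratios with different meanings (population-averaged and cluster-specific). Report the observed ICC with its scale.

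The analysis needs only a village or ASHA identifier on each record. The cost is somewhat wider confidence intervals, mainly for predictors that vary between villages. The sample size does not need to change for this point.
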